**Requirements for GCP informed consent**

GCP formal informed consent can only be requested when the subject is physically and emotionally well enough to receive and comprehend the details given to the subject in the information sheet and by the study worker. Due to the high likelihood of comprehension being impaired during an acute episode of ABM, it is not appropriate to take informed consent at the acute admission point. Once the subject has been stabilised, and has improved to a point where s/he has reasonable comprehension and retention of information, formal written informed consent will be requested. However the bundle will need to be started before informed consent can be obtained.

**No new drug or treatment is being tested that requires informed consent to administer**

The bundle consists of normal, recognised treatments, each with evidence of efficacy that do not require informed consent to administer in standard clinical practice.

**iv.viii Study monitoring and adverse events**

**Data monitoring**

A formal data monitoring committee is not required for this study, as the interventions being tested have individually been proven to be effective, and there is no blinded/randomised intervention. However [name] (Professor of Tropical Medicine, University of Oxford) has agreed to act as an independent study monitor and review monthly aggregated reports on all outcomes and SAEs. A Malawian study monitor is due to be appointed.

**Risk of serious adverse events**

As no new intervention is being tested, the study team will be familiar with all elements of the bundle, and will receive additional training by the PI in both safe administration of each element and awareness of the potential for harm. Therefore the risks to the participants associated with the study will be minimal. Each participant will be very closely monitored with regular clinical observations throughout the 6 hour study period, and any clinical deterioration (based on the medical alert system) will trigger a medical review with the PI. The PI will be available in person or by telephone during all study hours to discuss any problems or issues and to review any deteriorating participant. For problems out of hours the medical on call team will be called to review the participant. When a clinical deterioration is noted and managed, the PI will review in detail all of the case records of that participant.

**Process of detecting and reporting SAEs**

To ensure adverse events are detected at an early stage, monthly mortality figures will be sent to the trial monitor for review. This data will be aggregated over time to improve interpretation and monitoring. Any suspected or unexpected serious adverse events (SAE/SUE) will be discussed immediately with the PI, study nurses and clinical officer and a record form will be completed. A serious adverse event will be classified as an unexpected negative outcome, harm to a trial participant, or an occurrence that results in a complaint to the trial team from a participant or their carer, or from within the AETC team.

All SAEs and SUEs will be discussed by the principle investigator with the chief investigators and details given to the trial monitor with aggregated mortality data. IRB COMREC will also be given details of all SAEs. If deemed necessary by either the CI, IRB COMREC or the study monitor, recruitment will be paused, and a meeting of the trial steering committee (TSC) convened to discuss the SAE and any protocol changes that may need to be made.

1. **Study duration and timing**

The study is planned to recruit for 2 years in total and 3 years in total is allocated for all formal stages of training, planning, recruitment, analysis and dissemination of the results. The detail of the relevant allocated times is represented in the following Gantt chart.

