**Burden and risks to study participants**

The study participants will benefit from increased nursing care and it is estimated that the risk of harm from additional observations and clinical care is minimal. The elements of the bundle are all designed to improve patient care, and therefore will not impose a significant burden on the study subjects. The independent study monitor will oversee all monthly mortality figures and SAEs to monitor for any potential harm. Potential risks to the study participants include the following. If any occur a SAE/SUE will be triggered.

| **Potential risk** | **Remedial action** |
| --- | --- |
| Excessive administration of intravenous fluids leading to cerebral oedema | Careful monitoring, administration of diuretics, head elevation, further staff training and supervision |
| Excessive administration of anti-seizure therapy to control a short fit leading to respiratory depression | Airway management, oxygen, ventilation if necessary, further staff training and supervision |
| Damage to the lining of the nose during insertion of airway support when in coma | Removal of the airway and re-insertion with a smaller tube in the alternative nostril |
| Transfusion reaction during blood transfusion | Transfusion will be stopped and intravenous fluid and steroids will be given. Blood bank to be informed and given the transfusion details |
| Transmission of blood borne viruses during blood transfusion | Participant or carer to be counselled regarding the risks and benefits of transfusion. No transfusion will be given without consent. |

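### The SAE definition has no seriousness criterion, so a death or new disability attributed to meningitis need not be reported singly and is specified to reach the monitor only in aggregate

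*Protocol*

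**What the plan says.** Protocol, Process of detecting and reporting SAEs: "A serious adverse event will be classified as an unexpected negative outcome, harm to a trial participant". Anything that prompts a complaint to the study team also qualifies. The definition thus has three limbs (unexpected outcome, harm, complaint), and none refers to how serious the outcome is. An event that qualifies is discussed at once, recorded on a form and passed to the monitor, and "IRB COMREC will also be given details of all SAEs". Deaths have a different route: "monthly mortality figures will be sent to the trial monitor for review", and "This data will be aggregated over time to improve interpretation and monitoring".

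Protocol, Burden and risks to study participants, lists five foreseen risks, among them "Excessive administration of intravenous fluids leading to cerebral oedema" and respiratory depression after too much anti-seizure treatment. It says of the list: "If any occur a SAE/SUE will be triggered".

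Protocol, Risk of serious adverse events, has deteriorating participants reviewed by the principal investigator, who then goes through their case records. Protocol, Data monitoring, dispenses with a data monitoring committee and relies on an independent monitor who sees monthly aggregated reports of outcomes and SAEs.

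**The concern.** Seriousness normally decides whether an event is logged; expectedness and relatedness are judged afterwards. Here expectedness and attribution come first. With mortality put at 54% in the Executive summary, and with coma, seizures and confusion among the inclusion criteria, staff can readily regard a death or a falling GCS as the disease taking its course. Nothing then obliges them to file a report.

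This matters because the SAE report is the only individual-case route that the protocol defines to the monitor and the ethics committee, and the section describes the steering committee meeting that follows a pause as a discussion of the SAE. There is no data monitoring committee behind it. The protocol itself calls fluid resuscitation in this disease controversial for want of randomised trials, so case-level safety information on the bundle has real value.

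**Working it through.** The protocol gives no figure on this point to reproduce. The check is to apply the definition to typical events, look at the other channels, and then size the gap.

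**Step 1. Apply the definition.**

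| Event | Limb or trigger met | Single report required? |
|---|---|---|
| Complaint from a carer | Complaint limb | Yes |
| Nasal injury from an airway | Listed risk; also harm | Yes |
| Cerebral oedema or respiratory depression that staff attribute to excess treatment | Listed risk; also harm | Yes |
| Falling GCS, seizure or death that staff attribute to meningitis | None: not unexpected, not judged a harm, no complaint | No |
| New disability that staff attribute to meningitis | None | No |

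Rows 3 and 4 can have the same bedside appearance. What separates them is a causal judgement made before anything is filed.

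**Step 2. Look for another route to the monitor or the ethics committee.**

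- Hourly observations with GCS (Intervention design) and daily ward review (Follow up) detect events but do not report them. The ward review covers participants included on CSF results, so it does not cover those excluded on CSF after receiving the bundle.
- The principal investigator's review of deteriorations is internal. It is described for the 6-hour period, with the on-call team reviewing problems out of hours.
- The monitor's reports are aggregated. Data sharing also promises anonymous downloads each month but does not say whether they are at patient level.
- The ethics committee is promised SAE details. No mortality figures are promised to it in that section.

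**Step 3. Size.** Inputs: mortality 54% (Executive summary); 200 to 250 subjects, equally split (Sample size); two recruitment periods of 9 months (Gantt chart), 18 months in all.

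- Deaths in total: 0.54 × 200 = 108; 0.54 × 250 = 135.
- Per phase: 108/2 = 54; 135/2 = 67.5.
- Per month: 108/18 = 6.0; 135/18 = 7.5.

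**Step 4. How much aggregate mortality could show.** Illustration only, because the protocol states neither an alpha nor a harm to be detected. I assume a two-sided 0.05 comparison at the end of recruitment, n per phase of 100 or 125, p₁ = 0.54, and a true rise to p₂:

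power = Φ{[(p₂ − p₁) − 1.96 √(2p̄(1 − p̄)/n)] / √[(p₁(1 − p₁) + p₂(1 − p₂))/n]}, where p̄ = (p₁ + p₂)/2.

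For n = 100 and p₂ = 0.64: (0.10 − 1.96 × 0.06956)/0.0692 = (0.10 − 0.1363)/0.0692 = −0.525, so power = 0.30.

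| p₂ | n = 100 | n = 125 |
|---|---|---|
| 0.59 | 0.106 | 0.122 |
| 0.64 | 0.300 | 0.362 |
| 0.69 | 0.588 | 0.685 |

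A monthly look during recruitment has fewer subjects and so less power. Totals alone would often miss a moderate harm, which is why individual cases matter.

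**The case against.** The strongest reply is that the protocol separates the two tasks sensibly. Death is an endpoint with a high background rate, so it is followed in aggregate by an independent monitor, and single reports are kept for suspected harm. The harm limb is not qualified by the word unexpected, so foreseen harms count. The risk list makes the fluid and sedation harms triggers in any case. Any trigger that rests on causality carries some risk of misattribution. Much of this stands, and it rules out three stronger readings that a reader might infer.

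- *The named harms go undetected.* Not supported. They are explicit triggers, and hourly observations, daily ward review and the principal investigator's case review provide for detection.
- *There is no case-level record of what was given.* Not supported. Table 2 specifies a timed drug chart, repeated fluid-balance assessment and a seizure chart, and clinical data are captured electronically. The record exists; it is simply not attached to a report that leaves the site.
- *Harm cannot be compared between phases.* Not supported for the serious outcomes. Death, seizures and neurological disability are secondary endpoints at days 10 and 40, with identical data collection in both phases and planned between-phase tests, however an event is classified.

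It is also fair to say that the monitor is not blind to deaths, and that the chief investigator, the ethics committee or the monitor may have recruitment paused if they think it necessary. What the reply leaves open is the event seen at the bedside, put down to meningitis and never sent on as a case. Following endpoint deaths in aggregate does not require a definition under which a complaint is always an SAE and a death may not be.

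**Conclusion.** The concern holds as a gap in definition and reporting. The SAE definition has no seriousness criterion, and the listed triggers work only once staff have attributed an event to excess treatment. Deaths, life-threatening deteriorations and new disabilities attributed to meningitis therefore need no single report, and the protocol specifies only aggregated figures for them.

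The figure of 108 to 135 deaths is a ceiling, not a forecast. It assumes that 54% applies to everyone recruited and that no death meets any limb of the definition. The conclusion about the monitor would soften if the monthly downloads proved to be patient-level listings, but the protocol does not say so. The point should be corrected. It does not undermine the trial's endpoints.

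**What to change.** In Process of detecting and reporting SAEs:

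1. Define an SAE, in phases 1, 2a and 2b alike, by the seriousness of the outcome (death, threat to life, prolonged stay, new significant disability), whatever the presumed cause.
2. Record expectedness and relatedness as separate fields after the event is logged.
3. Log complaints and minor injuries separately.
4. Reconcile this section with the triggers in Burden and risks to study participants, so that both describe one system.
5. Send the monitor a periodic line listing by phase of deaths and serious deteriorations, with the treatments already charted. Make sure phase 1 has equivalent entries, since the Table 2 charts are specified for the bundle targets. Expected deaths, given their number and their role as an endpoint, can go by line listing and need not be expedited.

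Cost: protocol wording, a short form, and about 6 to 7.5 deaths a month to list. Non-fatal serious events, phase 2a participants and participants later excluded on CSF add to this. The protocol gives no numbers for them, so the full load on four nurses and one clinical officer cannot be stated. No clinical procedure changes.

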**Timetable**

1. November 2010-January 2011 Study set up in Malawi
2. Feb 2011-October 2011 Maternity leave
3. November 2011 Review of study set up so far.
4. Completion of data collection tools, SOPs and study logistics. Final equipment procured.
5. December 2011 Study staff start induction in the AETC, working as supra-numerary staff. Piloting of data collection tools, testing of all equipment and SOPS.
6. January 2012: Phase 1 prospective control recruitment starts
7. September 2012: Phase 1 recruitment ends.
8. September-December 2012: Phase 2a introduce and pilot the meningitis care bundle
9. January 2013: Phase 2b ( care bundle) recruitment starts to
10. September 2013: TSC meets to discuss Phase 2b results. Time allowed for continuation of 3-6 months.
11. December 2013: Study ends, results analysed. Further laboratory work completed.
12. May 2014 PhD write up, scientific papers and results analysis completed.

**Gantt chart of timetable/milestone reporting**

| **Study event** | **3 months** | **1 month** | **1 month** | | **9 months** | | **3 months** | | **9 months** | | | | **3 months** | | | | **9 months** | |
| --- | --- | --- | --- | --- | --- | --- | --- | --- | --- | --- | --- | --- | --- | --- | --- | --- | --- | --- |
| **Study setup** |  |  |  | |  | |  | |  | | | |  | | | |  | |
| **Final study organisation** |  |  |  | |  | |  | |  | | | |  | | | |  | |
| **Staff induction and pilot data collection** |  |  |  | |  | |  | |  | | | |  | | | |  | |
| **Phase 1** |  |  |  | |  | |  | |  | | | |  | | | |  | |
| **Phase 2a** |  |  |  | |  | |  | |  | | | |  | | | |  | |
| **Phase 2b** |  |  |  | |  | |  | |  | | | |  | |  | | |  |
| **Data analysis** |  |  |  | |  | |  | |  | | | |  | |  | | |  |
| **TSC meeting** |  |  |  | |  |  |  | |  |  |  |  |  |  | | |  | |
| **Milestone report** |  |  |  |  |  | |  |  |  | | | |  |  | |  |  | |

1. **Sample size**

In published data from resource rich hospitals, all EGDT studies have reported sample sizes from 100-500 in both cluster randomised and before/after designs. Two studies have demonstrated a mortality benefit with 100 subjects in each group using a before/after design (33-34). However it is unclear how this effect size can be translated to a resource limited African hospital, as no studies of EGDT in adults have been conducted in this setting and the ETAT paediatric data was retrospective with no sample size calculation.

We propose to recruit equal numbers of subjects in phases 1 and 2, and treat this study as pilot testing of EGDT. Using the projected timeframe I expect to recruit 200-250 subjects in total, equally distributed over phases 1 and 2. There is a risk with before/after studies that the design may over-estimate the actual size of any potential benefit from the intervention (39), and can be confounded by time. Therefore definitive conclusions as to the efficacy of the bundle can only be drawn from larger, cluster randomised parallel studies, and this study will provide preliminary proof of principle.

1. **Data collection and management**

**Clinical data**

Coded clinical data will be captured by the study nurses and clinical officer electronically into a secure electronic database using the ‘redcap’ system, and from there it will be transferred to statistical software. Patient identifiers will be used from the ‘Spine’ data recording system using barcodes, enabling data to be collected across multiple sites within QEH. See data confidentiality section for more detail on Spine page 23

Data will be imputed from the bedside into either a secure study laptop based in the AETC, or via a handheld computer (PDA) using a barcode reader, resulting in rapid and secure data collection. All data will be downloaded to the MLW secure server every 24 hours and will not be retained on the electronic devises to minimise the risk to confidentiality. No identifying details except the Spine data code will be retained in the database.

**Demographic data**

Basic identifying demographic data will be will be kept in a written record in a secure locked cabinet, separately from the main study database, and will provide a link to the barcode data. This is necessary to be able to text message/telephone study participants on a weekly basis to ensure the maximum survival information is collected for the study endpoints. This data will only be available to the study team and will be destroyed at the end of the study. No clinical data will be noted in this record.

**Target and bundle sustainability related data**

Data will be collected on a weekly basis by the nurses through feedback to the PI to assess if the AETC staffing and equipment levels would be appropriate to deliver targeted care. An assessment will be made with the assistance of a local health economist of the additional cost of implementing each element of the bundle (if proven to be effective) into long term practice.

1. **Data analysis**

Each element of the bundle will be analysed separately to calculate the percentage of each clinical target was achieved.

Analysis will be primarily by intention to treat, and then per-protocol. Data will be collected using ‘redcap’ electronically and then transferred to SPSS/PASW statistical programme and GraphPad5™ software for analysis.

**The following statistical tests will be used to compare the intervention and control groups.**

- Composite analysis of each proportion of target achieved
- Simple mortality proportions
- Kaplan-Meir survival analyses to establish the pattern of the death rate
- Chi squared tests and Fisher’s exact test will be used to analyse the significance of differences between the two phases of fixed endpoints.
- Logistic regression will be used to give an estimate of the size of the change in outcomes.
- Where appropriate the students T test and the Mann-Whitney test of medians will be used to compare the outcome between the bacterial loads in blood and CSF.

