***Secondary (to be measured at day 10 and day 40)***

1. Death
2. Persistent seizures requiring treatment
3. Significant neurological disability
4. Functional ability
5. Evidence of persistent renal injury
6. Blood and CSF bacterial load of *S. pneumoniae*

Death will be measured as a composite secondary endpoint (days to death/last known alive) using the following methods:

*Day 10 (acute)* – date of discharge (alive) or date of death will be recorded up to 10 days of inpatient antibiotic therapy.

*Day 40 (convalescent)* - Final outcome recorded ‘alive or dead’ following records from follow up or response to mobile telephone at until 6 weeks.

A history of seizures and functional ability since discharge will be taken, and endpoints 3-5 will be measured formally using the ***Modified Rankin score***, serum creatinine (to calculate eGFR), blood pressure and urine dip (for protein).

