**Sub-analyses will be undertaken of the following groups**

1. Patients presenting where death is predicted by the admitting clinician within the bundle implementation time period (6-8 hrs).
2. Subjects with normal CSF and an alternative diagnosis such as sepsis
3. Subjects with abnormal CSF but negative microbiological cultures and PCR.

4 weeks of statistician time is included in the budget. Data from this study will be aggregated with previously collected adult meningitis data from 3 previous studies in Blantyre to continue to study long term changes in meningitis mortality.

1. **Results Presentation**

The results will be presented in a variety of formats. Simple bar charts and pie charts will be used to compare the proportion of each target achieved with the EGDT. Kaplan-Meir survival graphs will be plotted for mortality analysis and the subjects from the two phases will be compared. The remaining outcome data will be presented in table format and displayed using bar charts. All results will be displayed in formats using GraphPad5™ software

1. **Results Dissemination**

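### Death is recorded as a censored time, but the only test and effect estimate named for it are binary, which misleads if lost patients are dropped and loss differs between phases

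*Protocol*

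**What the plan says.** The Endpoints section (iv.ii, secondary endpoints) states: "Death will be measured as a composite secondary endpoint (days to death/last known alive) using the following methods". It lists two readings. The day-10 reading is a date of discharge or death. The day-40 reading is a final alive-or-dead status "following records from follow up or response to mobile telephone at until 6 weeks".

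The Data analysis section lists the methods for comparing the groups. Those that bear on death are:

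- a crude summary: "Simple mortality proportions"
- a time-to-event display: "Kaplan-Meir survival analyses to establish the pattern of the death rate"
- two tests of significance, chi-squared and Fisher's exact, which "will be used to analyse the significance of differences between the two phases of fixed endpoints"
- a model for the effect size: "Logistic regression will be used to give an estimate of the size of the change in outcomes"

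The same section says "Analysis will be primarily by intention to treat, and then per-protocol". The Results Presentation section adds: "Kaplan-Meir survival graphs will be plotted for mortality analysis and the subjects from the two phases will be compared". No log-rank test, Cox model or Kaplan-Meier risk at a stated day is named.

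The Follow up section provides weekly text messages to a nominated telephone and a clinic visit at six weeks. The Transport section foresees patients who cannot attend and plans telephone attempts for them.

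**The concern.** The endpoint is set up to carry partial follow-up: a patient last heard from on day 20 contributes 20 days. The methods that carry the p-value and the effect size need a yes-or-no status at day 40 and cannot use that information. The only method listed that can use it is given a descriptive purpose.

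Missing status is also one-sided. Inpatients are reviewed daily and the hospital's electronic record holds discharge dates and cause of death, so deaths before discharge should nearly all be known. Unknown status arises among those who left alive. Removing them from a simple proportion takes out mainly survivors and raises the apparent mortality. If contact succeeds less often in one phase than in the other, part of that rise appears as a phase effect. Follow-up in the two phases runs about a year apart.

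What is at stake is specific objective 2, the relative reduction in mortality. The Sustainability section would turn a demonstrated mortality benefit into local treatment guidelines.

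**Working it through.** There is no mortality power figure to reproduce. The Sample size section gives expected recruitment of 200-250 in total, or 100-125 per phase.

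**Inputs**

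- Mortality 54%: Executive summary, Background. Treating it as day-40 mortality is an assumption.
- Dead before discharge 45% (45/54 = 83% of deaths): assumption.
- Hence discharged alive 55%, and dying between discharge and day 40: 54% − 45% = 9%.
- Loss L among those discharged alive, 10% to 30%, unrelated to fate: assumption. The protocol gives no rate.
- No bundle effect.

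**Formulas**

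- Lost patients dropped: (0.45 + 0.09(1 − L)) / (0.45 + 0.55(1 − L))
- Lost patients counted alive: 0.45 + 0.09(1 − L)

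| Loss L | Dropped | Counted alive |
| --- | --- | --- |
| 10% | 0.531/0.945 = 56.2% | 53.1% |
| 20% | 0.522/0.890 = 58.7% | 52.2% |
| 30% | 0.513/0.835 = 61.4% | 51.3% |

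**Phase comparison when the true difference is zero** (Phase 1 loss against Phase 2 loss)

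- 20% against 10%: dropping gives a false benefit of 2.5 points. Counting alive gives 53.1 − 52.2 = 0.9 points against the bundle.
- 30% against 10%: dropping gives a false benefit of 5.2 points. Counting alive gives 53.1 − 51.3 = 1.8 points against the bundle.
- Equal loss: the difference is zero under either handling. Only the mortality levels move.
- If Phase 2 has the greater loss, every sign reverses.

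**Type I error.** A simulation used 4,000 runs, 112 patients per phase, 54% mortality in both, 85% of deaths before discharge, loss unrelated to fate and a nominal 5% level.

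| Loss, Phase 1 / Phase 2 | Chi-squared, dropped | Chi-squared, counted alive | Log-rank |
| --- | --- | --- | --- |
| 20% / 20% | 4.4% | 4.8% | 4.7% |
| 20% / 5% | 8.7% | 4.9% | 4.7% |
| 30% / 10% | 12.5% | 5.1% | 4.8% |

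Under no effect, the Kaplan-Meier day-40 risk difference stayed within 0.3 points of zero in every loss pattern tried.

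**Equal loss with a true effect.** Take 54% against 40.5% (a 25% relative reduction), 20% loss in both phases and 90% of deaths before discharge. Dropping gives 59.0% against 45.5%, so the risk ratio moves from 0.750 to 0.771. Counting alive leaves it at 0.750.

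**Loss caused by death.** Suppose half of the post-discharge deaths are never reported and all survivors are followed. Counting those deaths as alive gives 0.45 + 0.045 = 49.5%. Censoring them at discharge gives a Kaplan-Meier risk of 0.45 + 0.55 × 0.045/0.505 = 49.9%. The truth is 54%, so censoring hardly helps here.

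**The case against.** The strongest reply is that the protocol already plans both kinds of analysis. Its day-40 reading is a binary status, which a chi-squared test fits. Kaplan-Meier stands under a heading about comparing the groups, and the curves of the two phases are to be compared. The fixed endpoints are not defined as day-40 death, since several other secondary endpoints are binary too. The test that goes with the curves and the coding of unknown status may be in a statistical analysis plan that is not shown. All of this stands, and the absence of a missing-status rule is not counted as a fault here. What remains is that the protocol does name a significance test and an effect estimate, and both are binary.

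A reader might infer that dropping the lost and counting them alive each bias the phase comparison in any event. The documents do not support that. Follow-up is planned to be identical in both phases, which makes equal loss more plausible, and equal loss unrelated to death leaves the null comparison unbiased. Counting the lost as alive does little harm in the ranges tried. Nor does the protocol say that lost patients will be dropped.

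A reader might also infer that censoring solves the problem. It does not if patients are silent because they have died, as the last calculation shows.

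Finally, death is secondary, the study is a declared pilot, and the spurious shifts are smaller than the sampling error. With 112 per phase the standard error of the risk difference is √(2 × 0.54 × 0.46/112) = 6.7 points. This limits the severity but does not remove the point, because the bias adds to that error and is avoidable.

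**Conclusion.** The point holds in a conditional form. The named test and effect estimate for mortality cannot use the last-known-alive date that the endpoint definition records. The resulting bias is material when two things coincide: lost patients are dropped, and loss differs between phases. Under the assumptions shown it is then 2.5 to 5.2 points, and simulated type I error at the unequal loss patterns tried was 8.7% to 12.5% instead of 5%. For scale, the protocol cites an absolute reduction of 9-10 points for septic shock, which is not a design effect of this study. With equal loss unrelated to death there is no bias under the null, and dropping only mildly attenuates the risk ratio when there is an effect.

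The loss rates and the share of deaths before discharge are assumptions; the documents give neither. The severity is modest: worth correcting, but not a threat to the primary endpoints, which concern target achievement.

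**What to change.** In the Data analysis section, base the day-40 mortality comparison on the Kaplan-Meier risk in each phase. Report the risk difference and risk ratio at day 40 with 95% confidence intervals and a log-rank test (or Cox model), censoring each patient at the date last known alive.

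Fix one time origin for day 40. The Follow up section equates six weeks with 40 days, while the Transport section counts six weeks from discharge, so a final status could be read at different times since admission.

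Keep chi-squared and Fisher's exact tests for endpoints with complete ascertainment, such as death before discharge.

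Because censoring assumes that loss is unrelated to fate, also report loss by phase and two bounds, with all lost patients dead and all lost patients alive.

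The cost is some wording and a little more analysis. No new data are needed, because the endpoint definition already calls for the dates.
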